### Confounding factors

There are a number of potential confounding factors in this study. These include surgical intervention received (i.e. skin grafting in the acute phase, spontaneous skin healing in the acute phase, post-acute reconstructive surgery), patient’s adherence to the treatment regime, whether all essential elements of the intervention were delivered by treating therapists (therapist fidelity), the pressure beneath pressure garments, and/or adverse events impacting on the allocated treatment.

Patient adherence and therapist fidelity will be monitored via self-report checklists of salient elements of the intervention. Therapist fidelity will also be evaluated through the use of audio recordings of 20% of patient sessions [45]. Pressure beneath pressure garments will be measured in millimetres of mercury (mmHg) at the garment skin interface using the Pliance X device [46]. An ICC of 0.998 has been reported for static measures of test-retest reliability and an ICC of 0.995 to 1.00 has been reported for inter-rater reliability of the Pliance X device [47].

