### Statistics

#### Sample size

The sample size estimate was calculated based on the primary outcome of scar thickness at 6 months post burn for one scar site. We assumed a pooled standard deviation of 1.0 mm based on a retrospective audit of data from our centre. To detect a statistically significant between-group difference of 0.76 mm in scar thickness with 80% power and an alpha value of 0.017 (due to three pairwise comparisons), 36 participants are required in each of the three groups. Assuming a 20% dropout, the total number of participants who need to be recruited at baseline is 135 (45 participants per group).

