#### Data analysis

Sociodemographic, clinical and intervention data will be summarised using descriptive statistics. For continuous outcomes either mean and standard deviation, or median and range will be used depending on the distribution of the variable. For categorical outcomes frequency and percentage will be reported. Data related to intervention benefits will be analysed on the ‘intention-to-treat’ (ITT) principle, defined as participants analysed according to their randomly allocated study group regardless of treatment received who complete follow-up data collection and who receive the recommended length of intervention. Data related to intervention adverse effects will be analysed according to the ITT principle as well as per protocol defined as those who received and commenced the intervention. A sensitivity analysis will be conducted to compare the ITT and per-protocol approaches if appropriate. Baseline characteristics will be compared to assess the compatibility of groups. At baseline between-group differences will be investigated using linear regression for continuous data and Fisher’s exact test for categorical data. Post-baseline, between-group differences in adherence will also be investigated using linear regression at each time point. Potential confounding variables for the primary outcomes are considered a priori to be: age, days to re-epithelialisation, percentage maximum burn depth, days post burn when scar management commenced, Fitzpatrick skin type, percentage TBSA burned, patient adherence, level of pressure beneath garment (for the groups treated with pressure garments), anatomical body site treated, surgical intervention received (skin grafting in the acute phase, spontaneous wound healing in the acute phase, post-acute reconstructive surgery), wound complications (e.g. infection), other interventions received (e.g. massage) including the use of medications for itch [8, 9, 48].

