The primary outcomes will be analysed using mixed effects regression analyses to examine differences at 6 months post burn, adjusting for the baseline value of the outcomes. Mixed effect regression analyses will be completed for each follow-up time point. Potential confounding variables that are identified as imbalanced between the groups will be entered into regression analyses. The time-varying covariates are patient adherence, level of pressure beneath garments, and other interventions received. All of the other potential confounding variables are non-time-dependent covariates. Sensitivity analyses will be completed for missing data using multiple imputation of missing observations by creating ten complete data sets [49] of missing dependent and independent data. For participants from whom data is collected from two scar sites, the multiple sites on these individuals will be accounted for in analytic models by including the scar site as a random effect nested within participant. Initially all participants will be included in the analyses. The analyses will then be repeated after stratifying by surgical intervention (i.e. skin grafting in the acute phase, spontaneous skin healing in the acute phase, post-acute reconstructive surgery). Subsequently, the influence of sociodemographic, clinical and intervention factors, and primary and secondary outcomes not included as dependent variables, on primary and secondary outcomes will also be examined using regression models. Differences in health-related quality of life between the intervention group and respective normative comparison groups will be analysed using *t* tests, z-scores, or equivalent nonparametric tests where appropriate. Differences in self-reported outcomes by children versus caregivers, between age groups and in comparison to normative data will also be examined using univariate statistics such as *t* tests, z-scores, or nonparametric equivalents. Significance will be set at less than 0.05. Data will be analysed using SPSS (SPSS Inc., Chicago, IL, USA) or Stata (StataCorp, College Station, TX, USA) where appropriate.

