## Discussion

Silicone products and pressure garment therapy have been accepted treatments for burn scar management in high-income countries for over 40 years, though there is minimal evidence to support their use [5, 7, 10, 13]. In addition, minimal research has been completed with a paediatric burns population or with any age group using a broad evaluation that investigates the effectiveness of scar prevention interventions, their impact on health-related quality of life, the burden of treatments on patients and their families, or the paediatric patient’s adherence to these interventions.

Whilst little is known about adherence to recommended wear and care regimes for children using topical silicone gel and/or pressure garments, adherence by children is likely less than optimal. In adults, adherence to recommended pressure garment therapy has recently been recorded as 15 to 80% with reasons for nonadherence including the cosmetic appearance of garments, insufficient education regarding garment use as well as poor fit and discomfort [50]. Low rates of adherence to recommended silicone gel sheeting use (24 h per day) have also been reported in adults [51]. It is expected that adherence will be greater when using topical silicone gel (Strataderm®) compared to pressure garment therapy due to its reduced application time and there being no need for additional care/maintenance of the product.

The burden of topical silicone gel also appears lower than pressure garment therapy due to recommended application of the product once or twice daily (depending on scar location), fast drying time and durability. However, topical silicone gels may be time-consuming to apply to an extensive body surface area and have been documented to cause local dermatological reactions [25]. Thus, further investigation of their effectiveness is required.

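### The imbalance rule makes adherence, garment pressure and later co-interventions eligible for the between-arm models, although they arise after randomisation and can be consequences of allocation

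*Protocol article*

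**What the plan says.** The Data analysis section of the protocol sets out an a priori list of potential confounders of the primary outcomes. Most entries are patient or burn characteristics. The list also holds patient adherence, "level of pressure beneath garment (for the groups treated with pressure garments"), and other treatments given alongside, with massage as the example and itch medication included.

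The section then describes the mixed effects model for the primary outcomes, adjusted for the baseline value, and adds the entry rule: "Potential confounding variables that are identified as imbalanced between the groups will be entered into regression analyses". The next sentence settles which of these change over time: "The time-varying covariates are patient adherence, level of pressure beneath garments, and other interventions received". All the others are declared not time-dependent.

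Two further statements bear on this. The same section plans to compare adherence between groups after baseline, at each time point. The Discussion predicts the result: "It is expected that adherence will be greater when using topical silicone gel" than when using pressure garments.

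**The concern.** Randomisation removes confounding of the arm comparison by anything that precedes it. A variable that comes into being afterwards, and that the arm influences, is part of how the treatment acts or a response to how the child is doing. Adjusting for it removes the part of the effect that runs through it. Where the variable also shares unmeasured causes with the outcome, adjusting can create a difference that does not exist.

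The entry rule aggravates this. Imbalance in a pre-randomisation factor is chance. Imbalance in adherence is what the protocol expects the treatments to produce. A rule that adjusts for whatever differs between arms therefore leans towards a variable on the treatment pathway.

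At stake is the meaning of the primary estimate. The Objectives ask which treatment is more effective, and the analysis is meant to keep children in their allocated group whatever treatment they actually got. A difference adjusted for adherence answers another question: how the arms would compare at equal adherence, and even that only under strong assumptions.

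**Working it through.** **1. Timing of each variable.** The Blinding section puts baseline measures before randomisation.

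| Variable | When it arises | Status in an arm comparison |
|---|---|---|
| Baseline outcome, surgical stratum, age, burn depth, burned area, skin type | Before randomisation | Legitimate |
| Adherence | Reported at 3 and 6 months (Patient adherence) | Consequence of allocation |
| Garment pressure | After a garment is allocated and fitted; also measured at 1 week (Study design) | Consequence of allocation; exists in two of three arms |
| Other treatments, itch medication | Declared time-varying | Legitimate if in use at baseline; later use can respond to the arm or to itch, a primary outcome |
| Wound complications | Declared not time-dependent | May precede randomisation; no fault shown |

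**2. The plan's own figures.** Inputs from Sample size: "between-group difference of 0.76 mm in scar thickness", SD 1.0 mm, 80% power and "an alpha value of 0.017 (due to three pairwise comparisons"), taken as two-sided.

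n = 2 × (2.387 + 0.842)² × (1.0/0.76)² = 36.1, which rounds up to 37 against the stated 36. Power at 36 per group is Φ(0.76/√(2/36) − 2.387) = 79.9%. Dropout: 36/0.80 = 45, and 3 × 45 = 135. The stated size reproduces and is not in dispute. It is the yardstick for what follows, in which all inputs not taken from the protocol are assumptions.

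**3. Would the rule pick adherence?** The protocol gives no criterion for imbalance. Assume a two-sided 5% test with 36 per arm: P(flag) = Φ(d/√(2/36) − 1.96), where d is the true arm difference in SD units.
- d = 0.25: 18%
- d = 0.5: 56%
- d = 0.75: 89%
- d = 1.0: 99%

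**4. Shift in the estimate.** Adjusted difference = total difference − (thickness change per unit adherence × arm difference in adherence), where one unit is the step from none to full adherence.
- Assume adherence of 85% against 50% and 1 mm less thickness per unit: 1.0 × (0.85 − 0.50) = 0.35 mm, which is 0.35/0.76 = 46% of the target difference.
- Range for 0.5 to 1.5 mm per unit and 10 to 50 points: 0.5 × 0.10 = 0.05 mm to 1.5 × 0.50 = 0.75 mm.
- Direction: if gel is better by 0.76 mm and has the higher adherence, adjustment gives 0.76 − 0.35 = 0.41 mm. If garments are better by 0.76 mm although worn less, it gives 0.76 + 0.35 = 1.11 mm. The shift can go either way.

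**5. Power, if the adherence pathway runs with the total effect.** With the difference reduced by the mediated share, 36 per group and alpha 0.017:
- 25% mediated: 0.57 mm, power 51%
- 50% mediated: 0.38 mm, power 22%
- 75% mediated: 0.19 mm, power 6%

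**6. A difference where none exists.** Simulation of two arms of 36 with no true effect (4,000 runs). The covariate shifts by 1 SD with arm and shares an unmeasured severity factor with the outcome. Severity loadings of 0.3, 0.5 and 0.7 give spurious adjusted differences of 0.09, 0.25 and 0.49 SD, and type I error of 2.5%, 8.0% and 39% against a nominal 1.7%. With a shift of 0.5 SD, type I error is 2.2%, 3.0% and 10.4%.

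**7. Garment pressure.** The Intervention section gives group 1 gel and no garment, so a model across all three arms has no pressure value for that group. The restriction to garment groups stands in the list of confounders but is not repeated with the entry rule or the time-varying covariates.

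**The case against.** Much can be said for the plan, and several stronger readings fail.

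- **Entry is conditional.** A reader might infer that these variables are in the primary model outright. They are not: the stated model adjusts for the baseline outcome, and the others enter only if imbalanced. This stands. It does not rescue the rule for adherence, where imbalance is predicted. For co-interventions and itch medication no between-arm test is described and no difference is predicted, so the point there is only that later use can depend on the arm.
- **Pressure is already limited to the garment groups.** This stands in part: the authors saw that it does not apply to gel alone. A reader might infer that the gel-only arm would drop out of the model, that pressure would be nearly collinear with arm, or that values would be invented. The protocol states none of these. What remains is that the restriction is not carried into the three-arm model.
- **Imputation.** The plan describes "multiple imputation of missing observations by creating ten complete data sets [49] of missing dependent and independent data", but as a sensitivity analysis, and nothing says it would cover a pressure that cannot exist. No fault is shown.
- **Regressing outcomes on other outcomes.** That step is introduced as a later, separate look at influencing factors and is not presented as an arm comparison.
- **Adverse events and complications.** The Confounding factors section mentions "adverse events impacting on the allocated treatment", but the a priori list for the primary outcomes leaves adverse events out. Wound complications may predate randomisation, since products are supplied only once the skin has healed.
- **The size is assumed.** This stands. The protocol cites adult adherence to garments of 15 to 80% but gives no link from adherence to thickness.

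**Conclusion.** The point holds and should be corrected before analysis. As written, the rule allows the randomised comparison to be conditioned on adherence, which the protocol expects allocation to change, and it leaves garment pressure and post-randomisation co-interventions eligible as well. If it is followed, the adjusted difference ceases to be the effect of assignment and conflicts with the aim of comparing children as allocated.

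The case is firmest for adherence. For pressure the gap is narrower, namely an unstated restriction in the three-arm model. For co-interventions and itch medication it rests on possible, not demonstrated, dependence on the arm.

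Neither size nor direction can be derived from the documents. The 0.35 mm shift, its range of 0.05 to 0.75 mm, and the power and type I error figures illustrate what could happen under the stated assumptions. A reader might take 46% as the share of the effect that would be lost; that needs the assumed adherence figures, the assumed slope and a pathway in the same direction as the total effect, and the protocol supplies none of them.

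**What to change.** In the primary and secondary between-arm models, restrict covariates to the baseline value of the outcome, the surgical stratum, and pre-specified prognostic factors fixed before randomisation. Co-intervention use or complications already present at baseline may qualify.

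Exclude from the imbalance-entry rule adherence, garment pressure, and co-interventions and itch medication used after randomisation. Report these by arm instead. Examine pressure only within the two garment arms, and adherence only in a separately labelled exploratory analysis.

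The cost is a change of analysis wording. No new data are needed, the sample size is unaffected, and the explanatory analyses can still be run under their own label.

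### Ten imputed data sets leave the missing-data sensitivity p-value sensitive to the random seed near the significance threshold; 100 would largely remove this at almost no cost

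*Protocol article*

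**What the plan says.** The Data analysis section of the protocol article makes a mixed effects regression the primary analysis at 6 months, adjusted for the baseline value of the outcome. It then states that "Sensitivity analyses will be completed for missing data using multiple imputation". The number is fixed, with a literature citation: "multiple imputation of missing observations by creating ten complete data sets". The imputation covers outcomes and covariates together ("of missing dependent and independent data").

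The Sample size section gives the expected loss: "Assuming a 20% dropout, the total number of participants who need to be recruited at baseline is 135". It uses an alpha of 0.017 for each of three pairwise comparisons, whereas the Data analysis section says "Significance will be set at less than 0.05".

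The same section limits the analysis of benefit to children who finish follow-up and receive the full course of treatment. The imputation is therefore the only stated analysis aimed at missing data. The planned comparison of intention-to-treat and per-protocol results serves a different purpose.

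**The concern.** Multiple imputation draws random values, so its pooled result carries simulation noise that shrinks as the number of imputations grows. With about a fifth of the 6-month outcomes missing, ten is a small number if the p-value is to be read against a threshold.

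Readers will set the imputed result beside the main one and ask whether the two agree. If the imputed p-value is near the threshold, the answer may turn on the seed instead of on the data. The article itself fixes the number, so the point concerns a stated figure and not a detail left to another document.

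**Working it through.** **Plan's own figures.** With a difference of 0.76 mm, SD 1.0 mm, alpha 0.017 (two-sided assumed, as sidedness is not stated) and 80% power, the normal approximation gives 37 per group when rounded up. Power at the stated 36 is 79.9%, so the figure reproduces within rounding. Then 36 / 0.80 = 45 per group and 3 × 45 = 135, as stated. At 20% loss, 9 of 45 children per group lack a 6-month value.

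**Inputs for the check.** The number of imputations is m = 10 (Data analysis). Dropout is 20% (Sample size). The fraction of missing information, FMI, is not given. About 0.20 is assumed from the dropout rate, with 0.10 to 0.50 as the range.

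**Formulas.** Relative efficiency is 1 / (1 + FMI/m). Monte Carlo error as a share of the standard error is about √(FMI/m).

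At m = 10:

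- FMI 0.10: efficiency 1/1.01 = 99.0%; error √0.010 = 10.0% of the standard error
- FMI 0.20: efficiency 1/1.02 = 98.0%; error √0.020 = 14.1%
- FMI 0.50: efficiency 1/1.05 = 95.2%; error √0.050 = 22.4%

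At FMI 0.20 the error falls to 10.0% with m = 20, 6.3% with m = 50 and 4.5% with m = 100.

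**Simulation of the p-value.** One pairwise comparison adjusted for baseline; 45 per arm, 9 missing per arm completely at random; baseline–outcome correlation 0.5 (assumed); regression imputation from arm and baseline; Rubin's rules with small-sample degrees of freedom. For each target, the arm effect in one data set was tuned so that 500 imputations gave the target p-value. That data set was then re-imputed 600 times at each m. The realised FMI was 0.19 to 0.22. The table calls the target the converged p.

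| Converged p | m | 5–95% range of p over seeds | Seeds with p > 0.05 |
|---|---|---|---|
| 0.05 | 10 | 0.025–0.097 | 55.8% |
| 0.05 | 100 | 0.040–0.063 | 48.5% |
| 0.04 | 10 | 0.020–0.081 | 33.2% |
| 0.04 | 20 | 0.023–0.068 | 28.2% |
| 0.04 | 50 | 0.029–0.055 | 14.2% |
| 0.04 | 100 | 0.033–0.051 | 6.8% |
| 0.03 | 10 | 0.014–0.064 | 14.5% |
| 0.03 | 100 | 0.024–0.037 | 0% |
| 0.01 | 10 | 0.005–0.025 | 0.2% |
| 0.01 | 100 | 0.008–0.014 | 0% |

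A separate simulation agreed. At a converged p near 0.04 it gave 33% above 0.05 with ten imputations and about 5% with 100; near 0.03 it gave 14% and 0.1%.

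The same happens at the sample-size alpha. For a converged p of 0.01, 18.7% of seeds exceed 0.017 with ten imputations and 0.2% with 100.

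Running the ten-imputation analysis twice with the same seed gave an identical p-value.

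**The case against.** The best defence is that ten is enough for what this analysis is mainly for. It is a sensitivity analysis, and the useful question is whether the contrast and its interval stay similar. At 98% efficiency they are well estimated: the seed noise adds about 0.20/10 = 2% to the variance. No decision rule is tied to the imputed p-value. This stands, and it keeps the point minor.

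The assumed FMI may also be too high. According to Study design, the primary outcomes are also measured at 1 week and 3 months. Suppose that children lost by 6 months have a 3-month value, that it enters the imputation, and that its partial correlation r with the 6-month value is 0.5 to 0.7 (an assumption). Then FMI = 1 − 1/(r² + (1 − r²)/0.8), which is about 0.16 to 0.11, and the error is about 13% to 11% of the standard error. Imputing covariates could move FMI either way and cannot be quantified from the document. The 0.10 to 0.50 range covers this uncertainty, and the conclusion survives at its lower end in weaker form.

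Three stronger readings are tempting but not supported:

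- A reader might infer that the check cannot be reproduced. It can: a recorded seed returns the same result exactly. A seed is program detail that a journal article normally leaves elsewhere, so its absence is no fault.
- A reader might look only at data sets with a converged p of 0.04 to 0.06, where one simulation put 42% of ten-imputation runs on the other side of 0.05, and blame all of it on ten. Much of that comes from the selection: at a converged p of exactly 0.05, 48.5% of seeds still exceed 0.05 with 100 imputations. The contrast at 0.04 is the fairer measure of what more imputations gain.
- A reader might infer that the primary result is in doubt. It rests on the mixed effects regression and not on this p-value.

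**Conclusion.** The point holds as a minor one. Nothing in the article is contradictory or numerically wrong here; a stated number is lower than it needs to be. With FMI about 0.20, ten imputations give a sound estimate and standard error but a p-value that depends noticeably on the seed when it lies near the threshold. At a converged p near 0.04 about one seed in three crosses 0.05, against about 5% to 7% with 100 imputations; near 0.03 it is about 14% against almost none. By a converged p of 0.01, crossing 0.05 is rare (0.2%), although crossing 0.017 is not.

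These sizes rest on assumptions that the document does not supply: FMI about 0.20, a baseline correlation of 0.5, data missing completely at random, and a single scar site. How often the trial would land near a threshold is unknown.

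**What to change.** In the Data analysis section, replace ten with 100 imputed data sets, and state that the Monte Carlo error of the pooled arm contrasts will be reported with the sensitivity analysis. An intermediate number helps less: at a converged p of 0.04, 20 imputations still leave 28% of seeds above 0.05 and 50 leave 14%.

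The cost is a little computing time on about 135 children. Design, recruitment, data collection and the primary analysis are unchanged.

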### Significance of the study

This study will provide evidence of the effectiveness of three burn scar interventions for the prevention and management of burn scars in children. Specifically, evidence will be obtained regarding the effectiveness of topical silicone gel alone, pressure garment therapy alone, and a combination of topical silicone gel and pressure garment therapy. Future randomised control trials will be required to confirm these results; however, if consistent results are achieved, changes in clinical practice may occur.

By using a broad evaluation framework in combination with a design that carefully controls for confounding factors and investigates influencing factors, this study may determine which children benefit most from the scar management interventions of interest. Cost-effectiveness from a health service perspective will also be examined, which, to the knowledge of the authors, has not been examined in scar management intervention studies to date. Examining and controlling for the influence of a range of potential confounders will maximise the rigour of the study and will inform future studies of the factors that influence scar outcomes. Whilst this study will follow patients up to 6 months post burn, it study will pave the way for similar studies with follow-up to scar maturation (which can extend to 18 months post burn or longer) and multicentre trials.

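### Separate significance tests within each surgical stratum do not test whether treatment effects differ between strata; an arm-by-stratum interaction does

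*Protocol article*

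**What the plan says.** The Data analysis section of the protocol article first analyses all participants with mixed effects regression. It then states: "The analyses will then be repeated after stratifying by surgical intervention". The categories are "skin grafting in the acute phase, spontaneous skin healing in the acute phase, post-acute reconstructive surgery", and the Study design section uses the same factor to stratify the randomisation. The section ends with a general level: "Significance will be set at less than 0.05". No separate level and no exploratory label is attached to the stratum repeats, and no arm-by-stratum term is mentioned.

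The Sample size section covers only the overall pairwise comparison for thickness: a "between-group difference of 0.76 mm in scar thickness", "with 80% power and an alpha value of 0.017". The Significance of the study section says, in general terms, that "this study may determine which children benefit most from the scar management interventions of interest".

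**The concern.** Whether one surgical group benefits more than another is a question about the difference between stratum-specific arm effects. Repeating the analysis in each stratum tests something else: whether each stratum's effect, taken alone, differs from zero. A p-value below 0.05 in grafted children and above 0.05 in reconstructed children is not evidence that the effects differ. With small strata, and more so with unequal ones, that pattern can arise from a common effect.

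At stake is a conclusion that a scar treatment works in one surgical group and not in another when the trial shows no such difference. That would bear directly on which children are offered which treatment.

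**Working it through.** **Inputs from the documents.** Difference 0.76 mm; SD 1.0 mm ("We assumed a pooled standard deviation of 1.0 mm"); alpha 0.017; power 80%; 36 evaluable per arm; 20% dropout; three arms at 1:1:1; three strata; two primary outcomes; general level 0.05 (taken as two-sided).

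**Assumed.** The documents give no stratum sizes. I take 12/12/12 evaluable children per arm as the base case, with 20/12/4 and 16/14/6 as a range. Each sums to 36.

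**1. The plan's own figure.** n = 2(z₁₋α/₂ + z₀.₈)²/(0.76/1.0)² with alpha 0.017 gives 36.09 per arm, in line with the stated 36. 36/0.8 = 45 per arm, and 3 × 45 = 135. This reproduces.

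**2. Power within one stratum.** Two-sample t-test, unadjusted, noncentrality 0.76·√(n/2), df = 2n − 2:

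| n per arm | power at 0.05 | power at 0.017 |
|---|---|---|
| 4 | 15% | 6% |
| 6 | 22% | 11% |
| 12 | 43% | 26% |
| 20 | 65% | 47% |

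**3. A uniform effect seen through separate tests.** Suppose one pair of arms differs by 0.76 mm in every stratum. The strata contain different children, so the tests are independent. With stratum powers p₁, p₂, p₃:

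P(mixed) = 1 − p₁p₂p₃ − (1−p₁)(1−p₂)(1−p₃)

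- 12/12/12 at 0.05: 1 − 0.429³ − 0.571³ = 1 − 0.079 − 0.186 = 0.735.
- 20/12/4 at 0.05: 1 − (0.649 × 0.429 × 0.149) − (0.351 × 0.571 × 0.851) = 1 − 0.042 − 0.171 = 0.79.
- 16/14/6 at 0.05: 0.76.
- At 0.017 the three splits give 0.58, 0.63 and 0.60.

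A simulation using the SD pooled over the three arms in each stratum gives 74–79% at 0.05 and 60–64% at 0.017. All three strata are significant in only about 4–9% of trials at 0.05.

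**4. No effect anywhere.** Three pairwise tests in one stratum at 0.05, sharing arms, give at least one positive with probability about 0.12 (simulated). Over three independent strata: 1 − (1 − 0.12)³ ≈ 0.32 for one outcome. At 0.017 per test the single-stratum figure is about 0.044, so 1 − 0.956³ ≈ 0.126, or 12–13%. The result hardly changes across the three splits.

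**5. What the interaction test can do.**
- *Two strata of 12 per arm.* The difference between their pairwise effects has SE = √(4 × 1.0²/12) = 0.577 mm. Power for a 0.76 mm difference is Φ(0.76/0.577 − 1.96) = 26%. The difference detectable with 80% power is (1.96 + 0.84) × 0.577 ≈ 1.62 mm.
- *Full 4-df test.* Suppose one arm differs by 0.76 mm in a single stratum of n per arm. The noncentrality is 0.76² × (2/3) × n × (1 − n/36). With n = 12 this is 3.08, and power is 24%. It is 26% if that stratum has 20 or 16 per arm, and 13–16% if it is the smallest stratum (4 or 6 per arm).
- *False-positive rate.* 5% per outcome, against about 32% for the nine separate tests at 0.05.

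**The case against.** **The article does not tie the stratum repeats to the question of who benefits most.** This stands. The Significance section attributes that hope to the evaluation framework and to the study of influencing factors in general. It is worded as a possibility, and the same section says further trials are needed for confirmation. The Objectives state no subgroup hypothesis. A reader might infer that the trial intends to name a best-responding surgical group by comparing p-values; the text does not say so. However, the regression of outcomes on clinical and other factors that follows the stratum repeats describes association with outcome, not effect modification. No analysis in the text therefore addresses differential benefit.

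**A false subgroup claim is not shown to be likely.** This also stands. A reader might infer it from the 74–79%, but that is the chance of a misleading pattern under a uniform effect, and a pattern becomes a claim only through reporting. With no effect, the figure for thickness is 32%, and 12–13% if the sample-size alpha of 0.017 were carried into the analysis. With one omnibus test per stratum at 0.05 it would be 14%. Counting both primary outcomes gives about 53%, but only if itch and thickness are independent, which is doubtful in the same children.

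**An unseen analysis plan may add an interaction test.** It may, and its absence from an article would not by itself be a finding. The point rests on what the article does fix: separate repeats and a 0.05 threshold.

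**The subgrouping is legitimate.** Agreed. It is one prespecified factor, it is the randomisation stratum, and it comes after the overall analysis. The fault lies in the inference, not in looking.

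**The power figures are rough.** Agreed. Baseline adjustment and a second scar site could raise them, and stratum sizes are assumed.

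**Conclusion.** The point holds in a limited form. The method written down cannot show that arm effects differ between surgical strata, whatever the stratum sizes. The size of the problem depends on assumed splits of 36 evaluable children per arm, an SD of 1.0 mm and unadjusted two-sided t-tests on thickness. On those terms a uniform 0.76 mm effect would look inconsistent across strata about 74–79% of the time at 0.05, and 58–63% at 0.017 (t-test calculation). The null false-positive rate is about 32% for one outcome at 0.05. These figures do not establish that a false claim is likely, nor that the authors plan one. The overall primary comparison is not affected.

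**What to change.** For each primary outcome at 6 months, add one arm-by-surgical-stratum interaction test to the all-participant mixed model, with the stratum main effects included. Report the stratum-specific arm differences with confidence intervals from that model, label them exploratory, and make no within-stratum significance claims. Base any statement on differential benefit by surgical group on the interaction. Keep the overall arm comparison from the model without the interaction term.

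State the low power openly: about 25% for a 0.76 mm difference with equal strata, with about 1.6 mm needed for 80% power between two strata of 12 per arm. A non-significant interaction would therefore not show that the effects are equal. Soften the remark in the Significance section accordingly.

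The cost is wording and one extra model term per outcome, using the same data and software. The drawback is that the trial will probably be unable to say which surgical group benefits most; the present plan cannot say so either.
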